#### Cost-effectiveness analysis

The cost-effectiveness assessment will focus on the complete package and then separate, principal components including health, immunization, and nutrition interventions. The costing methodology will be activity-based, with distinct implementation costs. The costing data will include community engagement, mobile health services, and private practitioner engagement. Costs incurred, incremental costs, costs averted, and predicted and identified change in health, immunization and nutrition outcomes will inform the analysis.

### Analysis

All data is captured electronically using customised applications running on android based handheld devices. Data is hosted at the Aga Khan University data center. Demographic, clinical, knowledge, attitude & practices (KAP), and MNCH related indicators data will be compiled and analyzed using STATA -version 17.0 [14].

Descriptive and inferential statistics will be used to characterize the study sample and test hypotheses. Descriptive results for all continuous variables (e.g., age) will be presented as mean ± standard deviation or median with inter-quartile range, while numbers (percentage) will be reported for all categorical variables.

To assess the independent effect of intervention, propensity score matching was employed to identify similar UCs based on geographical location of UC, population density, size of under-five population, number of health facilities and health workers, and immunization coverage. Through this process, three matched UCs are also surveyed. Among the predictors, exact matching has been enforced to achieve the balance for all predictors between the intervention and non-intervention groups.

We will calculate overall and region-specific health coverage at baseline, midline, endline and at close-out for both intervention and control group. The mean and percentage point difference in coverage between baseline and endline, and baseline and close-out will be estimated using a mixed effects linear regression model. Effect estimates will be reported with 95% confidence intervals. The clustered nature of the data will be accounted for by including each cluster as a random effect. Estimates will be adjusted for survey design and sampling weights by treating each UC as strata and clusters as primary sampling units.

Costing data for the *Naunehal* program will be collected based on a standardized template developed by J-PAL [15]. It will be explicitly mentioned what costs are being recorded including project administration, training, implementation, goods purchased, and monitoring. The costs will be measured with the consideration that *Naunehal* is a pilot project and scaling up the project may change actual costs. Base Year and Year of Analysis will be accounted for including inflation costs and exchange rates. The cost-effectiveness will be assessed on basis of number of beneficiaries reached and the program effect on key indicators, followed by determining the cost-effectiveness ratio.

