### Study design

The project adopts a quasi-experimental prepost study design to assess the impact of the proposed interventions. The three UCs are the intervention sites and for each of these target UCs, a separate, matched control UC of comparable size, population, location and coverage indicators was identified, with propensity score matching and in consultation with local partners. The matched UC was always in the same district but never bordering the target UC. Baseline, midline endline, and close-out surveys will be conducted using the 30x7 techniques. Thirty clusters demarcated by the government’s polio program from each UC are randomly selected and 15 households with children under-five selected from each cluster. Thus, to achieve an optimal sample size, 450 households are surveyed from each of the intervention and control UCs (Table 1). The surveys focus on household characteristics, immunization coverage, health & care seeking behaviours, especially in the COVID context, and water, sanitation, and hygiene (WASH) practices.

**Table 1 pone.0287722.t001:** Sample size for household survey by UC.

Sr No.	District	Sample Size (Households)
1.	UC in Quetta	450
2.	UC in Peshawar	450
3.	UC in Lakki Marwat	450
4.	Matched control UC in Quetta	450
5.	Matched control UC in Peshawar	450
6.	Matched control UC in Lakki Marwat	450
Total		2,700

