#### Intervention strategies

*Naunehal* aims to improve health service delivery and enhance uptake, by focusing on four main intervention strategies implemented in all three target UCs; community mobilization to enhance awareness and demand, mobile health teams offering MNCH and immunization services, engagement of private sector to increase immunization coverage and testing of a comprehensive health, nutrition, growth, and immunization app, *Sehat Nishani*. The target group of the project include women of reproductive age (WRA) (15–49 years) and children under-five residing in the UCs.

**Community engagement and mobilization** includes dissemination of comprehensive messaging on promotion of routine childhood immunization, optimal infant and young child feeding (IYCF) practices, handwashing, best possible sanitary practices, COVID-19 prevention, optimal diarrhea management, and appropriate care seeking for both pregnant women and young children. The messages were communicated via health promotion materials, health awareness sessions, and mosque announcements. Announcements especially encouraged the community for routine childhood immunization and to utilize *Naunehal* mobile health services and visit private practitioners’ clinics or government facilities for immunization. An integral step of the community engagement process was to map and consult with opinion leaders and influential community members, to introduce the project and gain their support for the activities.

**Mobile health services (MHS)** were deployed in each of the three pilot UCs, with *one team per UC* in the pilot phase. Each mobile team had *a female physician*, *a female vaccinator*, *and a facilitator* and visited pre-determined areas of the UC daily, for 06 days per week for 12 months. The locations kept rotating, with an effort to focus on hard-to-reach areas where access to and coverage of health facilities is limited. The team ensured that all COVID-19 -prevention recommendations of the government are followed.

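### The package is allocated by union council, but the planned confidence interval for its effect counts only variation between clusters inside union councils, so it is too narrow whenever union councils change differently for reasons unrelated to the package

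*Protocol article*

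**What the plan says.** Allocation is by UC. The Study design section states: "The three UCs are the intervention sites and for each of these target UCs, a separate, matched control UC" was identified. The Intervention strategies section describes "four main intervention strategies implemented in all three target UCs", so the package does not vary within a UC. On pairing, Study design adds: "The matched UC was always in the same district but never bordering the target UC".

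A cluster is something smaller than the unit of allocation: "Thirty clusters demarcated by the government’s polio program from each UC are randomly selected and 15 households with children under-five selected from each cluster". With 30 clusters in each of six UCs there are 180 clusters per survey round, but only six allocated units in three pairs.

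The Analysis section fixes the variance structure: "The clustered nature of the data will be accounted for by including each cluster as a random effect", and estimates are adjusted for the survey design "by treating each UC as strata and clusters as primary sampling units". Changes from baseline to endline and from baseline to close-out come from a mixed effects linear model with 95% confidence intervals. The same section gives the isolation of the intervention's own effect as the reason for matching, and the Introduction presents the project as a model that government could take up. The article contains no UC-by-round term, UC-level or paired analysis, or small-sample correction, and no statement that inference stops at these six UCs.

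**The concern.** Whatever happens to a whole UC between two survey rounds is shared by all its households and all 30 of its sampled clusters. Only one mobile team served each target UC, so even team performance cannot be separated from the UC. A model whose only random term is the cluster, with UCs as strata, sees none of this as error. Sampling more clusters or households shrinks the reported interval but does not reduce this component.

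Stable differences in level between UCs cancel in a baseline-to-endline contrast. What remains uncounted is variation between UCs in their change. If it is not zero, every effect interval is too short and the nominal 5% test rejects too often. The cost-effectiveness ratio would inherit the overstated precision, because it is built on the programme effect.

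This is not detail left to an unseen analysis plan, because the article itself specifies the variance structure.

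**Working it through.** **The plan's own figures.** 30 clusters × 15 households = 450, which agrees with the statement that "450 households are surveyed from each of the intervention and control UCs"; 6 × 450 = 2,700, the total in Table 1. Both reproduce. The documents give no power calculation, effect size, intracluster correlation or between-UC variance.

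**Assumptions (not in the documents).** Coverage p = 0.5; design effect 2; separate samples at baseline and endline; effect taken as the difference in change between target and control UCs; no true effect. Let s be the SD of UC-specific change and r the correlation of change within a matched pair.

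**Planned standard error.**
- Variance of one UC's coverage in one round: v = 0.25 × 2 / 450 = 0.001111.
- Two rounds, three UCs per arm: SE = √(4v/3) = √0.001481 = 0.0385.
- 95% half-width = 1.96 × 0.0385 = 0.075, or 7.5 points.

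**Standard error with variation in UC change.** SE = √(4v/3 + 2s²(1 − r)/3). The true type I error of the planned test is 2 × [1 − Φ(1.96 × 0.0385 / SE)].

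| s (points) | SE, r = 0 | Type I, r = 0 | SE, r = 0.5 | Type I, r = 0.5 |
|---|---|---|---|---|
| 0 | 0.0385 | 5.0% | 0.0385 | 5.0% |
| 2 | 0.0418 | 7.1% | 0.0402 | 6.0% |
| 3 | 0.0456 | 9.8% | 0.0422 | 7.4% |
| 5 | 0.0561 | 17.9% | 0.0481 | 11.7% |
| 10 | 0.0903 | 40.3% | 0.0694 | 27.7% |

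**Half-width of a UC-level interval at s = 5 points.**
- Three against three, t on 4 df, r = 0: 2.776 × 0.0561 = 0.156, or 15.6 points.
- Three pairs, t on 2 df, r = 0.5: 4.303 × 0.0481 = 0.207, or 20.7 points.
- Three pairs, t on 2 df, r = 0: 4.303 × 0.0561 = 0.241, or 24.1 points.

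**Simulation check.** A separate simulation (4,000 runs per setting, p = 0.5, intracluster correlation 0.05, hence design effect 1 + 14 × 0.05 = 1.7, r = 0) gave rejection rates for the planned test of 5.1%, 7.1%, 11.0%, 20.3% and 35.9% at s = 0, 2, 3, 5 and 8 points. The formula gives 5.0%, 7.5%, 10.7%, 19.9% and 34.9% for the same inputs. UC-level t tests, on 4 df or 2 df, stayed between 4.9% and 6.1%.

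**The case against.** The strongest reply is that the strata-and-PSU statement is correct survey practice. Clusters were sampled within six named UCs, and for coverage and its change in those UCs this is the right variance. That stands. A reader might infer that the sentence is wrong in itself, but the documents do not support that. The fault lies in carrying this variance over to the intervention effect.

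A reader might also infer that false-positive rates are well above 5% as a matter of fact. The documents cannot show this, since they give no between-UC variance. At s = 0 the planned interval is right, and at 2 points the inflation is mild.

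Matching matters too. Controls share the target's district and were matched on immunization coverage among other features, so district-wide shocks may largely cancel within a pair. The r = 0.5 column shows how much that could help. It reduces the inflation but removes it only if matched UCs change in step.

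It would be tempting to give the loss simply as 24 points, about 3.2 times the planned half-width. That figure takes no gain from pairing in the variance and yet pays its full cost in degrees of freedom. The 15.6-point interval on 4 df, about 2.1 times as wide, is equally defensible.

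Finally, the target UCs were chosen for their risk, neither randomised nor sampled. A paired t-interval therefore does not license generalisation either, and there is no compelling case for making it the sole primary inference or for barring every test of effectiveness. The planned region-specific coverage may already go part of the way to a pair-by-pair display. None of this makes the cluster-level interval adequate for the intervention effect.

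**Conclusion.** The point holds in conditional form. The package is allocated to three UCs against three, and the stated interval for its effect omits between-UC variation in change, with nothing elsewhere in the article to repair this or limit the inference. The interval is too narrow whenever that variation is not zero; by how much cannot be settled from the documents.

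Under the assumptions above, true type I error at an SD of 2 to 10 points is about 7% to 40% with independent UC changes and about 6% to 28% with a within-pair correlation of 0.5. The project's pilot status softens how far its claims reach, but the stated aim is still to estimate the effect of the intervention.

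**What to change.** In the Analysis section:

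1. Report the three pair-specific differences in change (target UC minus its matched control) side by side.
2. Add a UC-level analysis of the intervention effect with a small-sample reference distribution. It may be paired (2 df), three against three (4 df), or a mixed model with UC-by-round random effects and a small-df correction. Name the choice.
3. Keep the cluster-level mixed model, and state that its interval is conditional on these six UCs, excludes between-UC variation in change, and does not by itself support generalising to other UCs.

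No new data are needed. The cost is some analysis wording, one small table, and a wider, less favourable interval.

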### Ethics and dissemination

Ethics approval was obtained from the SickKids Research Ethics Board (#1000072563), and National Bioethics Committee (#NBC-561) based in Pakistan. Informed consent is obtained from all survey respondents i.e. the parents or guardians of under-five children. Importantly, No Objection Certificates (NOCs) were secured from authorities in Balochistan and KP. Community buy-in and support for the project is pivotal to its success. Meetings with community elders and leaders were held at the three study sites. During these meetings, the project team explained the purpose of the study and the schedule of activities. The team listened to community concerns and worked to address them during discussions and incorporated feedback where possible. These meetings not only increased community support for the project but were essential in securing the safety of project team in the area. Engaging government stakeholders was also an important aspect of our project as we aimed to implement delivery systems that would be sustainable by the government for future work. Inception meetings were conducted with provincial stakeholders including the Health and Finance Minister of KP, Chief Secretary of KP, Director General Health of Balochistan and the Pakistani Pediatric Association. Findings from the study will be disseminated through peer-reviewed journal publications and shared with key stakeholders who have been engaged in this project including government officials, and the Pakistan Pediatric Association.

## Discussion

*Naunehal* aims to test a low-cost simplified model of working in challenging areas that has the potential to be sustainably implemented. As well, this study is one of the first to systematically engage private health practitioners in Pakistan to deliver vaccinations to the community.

Although this is not a clinical study, there has been patient-health worker interaction within the mobile health services and private sector engagement. The baseline survey and initial pre-implementation engagement with community leaders and stakeholders informed the community engagement plan, the health promotion materials and the sites and schedule of the mobile health services. At the conclusion of the study, results will be shared with the community members through community-based dissemination and stakeholder acknowledgement events. A limitation of the study is that surveys may not capture the underlying reasons as to why the receptiveness to vaccination may change.
